Based on this rationale, we have shifted our outcome variables of interest for our pilot study using CRT as a pre-treatment intervention. Traditionally, the outcome variables for CRT are changes in cognitive flexibility. While important, we hypothesize that CRT may have more immediate positive impacts that will support its potential as a pre-treatment intervention [48]. We will examine whether CRT combined with a novel parental portion can positively impact behavior post-discharge. We hypothesize that CRT during a hospital stay will increase treatment engagement, increase rate of weight gain post-discharge, reduce symptom accommodation, and increase behavioral flexibility in adolescents and parents. As the site for this research is a medical unit with no psychosocial interventions, we opted to conduct a pilot and feasibility randomized control trial to pilot study procedures and refine the protocol prior. Doing so allows us to evaluate the feasibility (including burden for staff and parents and the acceptability of the treatment) of conducting CRT with a parent component on a medical unit and determine what changes may need to be made for a fully powered trial [49, 50].

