Main idea	1–8	Reading increasingly difficult text selections and summarizing the main idea in a short sentence	CC
Qbitz	1–8	Completion of a puzzle with small wood blocks designed to increase manual dexterity and encourage a variety of problem solving approaches.	CC and SS
Rebus	1–8	Visual or pictorial representations of common words, phrases, or idioms. Uses verbal and perceptual skills.	SS and CC
Set	1–6	Creation of sets using features of objects that are similar in specific ways	SS
Map	7–8	Encourages participants find different ways of navigating a map, utilizing verbal and spatial abilities, organizational skills, combining elements of set-shifting and central coherence	CC and SS
Homework review	2–8	Review tasks completed and link to what has been happening in CRT sessions	
Review of parent session	3, 5, 7	Review tasks that have been completed, and review the overall process of TTP or FFT	

*SS* set-shifting, *CC* central coherence

*Motor task in which adolescents can, in a very short period, see how practice can improve performance. It has an element of shifting as the task must be completed with each hand. This task also helps to teach implicit learning and highlight the importance of non-verbal learning and fluidity

**Table 2 Tab2:** Train the parent and Family Fun Time session-specific tasks

Session no.	Train the Parent (TTP) tasks	Family Fun Time (FFT) tasks
1	Introduction to CRT + TTP Illusion task Infinity signs Stroop Geometric figure	Introduction to Family Fun Time I Learn About You—You Learn About Me (favorite TV show) Coloring: color and switch Table topics Family choice
2	Review and update Illusion task Infinity signs Geometric figure Main idea	Review and update I Learn About You—You Learn About Me (listen to favorite song) Coloring: color and switch Table topics Family choice
3	Review and update Illusion task Infinity signs Main idea Qbitz	Review and update Mad Libs Table topics Sudoku Family choice
4	Review and update Illusion task Infinity signs Hand task Qbitz	Review and update Table topics Jenga *or* Apples to Apples UNO *or* Sudoku Coloring *or* Mad Libs Family Choice

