### Randomized groups

#### Cognitive remediation therapy and Teach the Parent (TTP)

This parental involvement addition to CRT is designed to increase parents’ understanding of their adolescent’s thinking styles and reinforce what the adolescent learns about their own style. We hypothesize that by including parents, they will be more likely to challenge eating disorder behaviors and be less likely to accommodate behavioral symptoms of the eating disorder (e.g., make something low-fat for dinner because the adolescent will not be as upset and agrees to eat the low calorie food). In TTP, adolescents receive their own treatment manual to use during their CRT sessions with their parents. Adolescents do tasks with their parents that they have already done with study staff. Adolescents are instructed to explain the rationale for CRT, what they have learned, and do four tasks with their parents. Table 2 lists the tasks done during each TTP session. The family is instructed to refrain from speaking about the eating disorder during CRT. TTP sessions occur up to four times (every other CRT session). A research assistant will be on hand to observe the session and ensure that the adolescent presents at least two tasks to parents. However, the research assistant will not engage with the family.

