### Blinding and randomization

The adolescent and at least one parent are required to participate in the study. After baseline assessment is completed (see Table 4 for measurement schedule according to the SPIRIT guidelines [53, 54]), the adolescent is randomized to a condition. Research assistants completing the baseline assessment are therefore blind to the condition at baseline.

**Table 4 Tab4:** Schedule of enrollment, intervention, and assessment

Study period													
	Enrollment	Baseline		Randomization	CRT sessions/intervention	Discharge		4 weeks post-discharge		3 months post-discharge		6 months post-discharge	
Timepoint	− t_1_	T_1_		T_1a_	Up to 8 sessions No assessment	T_2_		T_3_		T4		T5	
Enrollment													
Eligibility screen	X												
Informed consent	X												
Randomization				X									
Intervention													
CRT + TTP					X								
CRT + FFT					X								
TAU					X								
Assessments													
		*Adol.*	*Par.*			*Adol.*	*Par.*	*Adol.*	*Par.*	*Adol.*	*Par.*	*Adol.*	*Par.*
*Diagnostic/symptom tracking*													
EDE [55]		X								X			
EDE-Q [70]		X						X		X		X	
EDE-SF [52]		X				X		X		X		X	
ABOS [71]			X						X		X		X
BASC-2[72]		X	X					X	X	X	X	X	X
Weight and height								X		X		X	
*Medical chart review*													
Weight history		X											
Current weight		X				X		X		X		X	
Hormone levels		X								X		X	
Vital signs		X				X		X		X		X	
Daily caloric intake		X				X				X		X	
*Neuro-psychological*													
WASI (2 scale) [73]		X	X										
D-Kefs [74]		X	X							X	X		
BRIEF [75]		X	X					X	X	X	X	X	X
Hayling [76]		X	X							X	X		
Rey-O [77]		X	X							X	X		
Brixton [76]		X	X							X	X		
Line bisection [78]		X	X			X	X	X	X	X	X	X	X
PennCNB [79]		X	X									X	X
*Questionnaire*													
C/E [80]		X	X			X	X						
MSCARED [81]		X	X			X	X	X	X	X	X	X	X
EDQoL [82]		X				X		X		X		X	
DBS [83]		X				X		X		X		X	
CFS [84]		X	X			X	X			X	X	X	X
DFlex [85]		X	X			X	X	X	X	X	X	X	X
C-FOCI [86]		X				X				X		X	
YBC-EDS-SRQ [87]		X						X		X		X	
AFQ-Y [88]		X								X		X	
AAQ [89]			X						X		X		X
AESED [90]			X						X		X		X
BIS/BAS [91]		X	X					X	X	X	X	X	X
PAAQ [92]			X						X		X		X
DASS-21 [93]			X						X		X		X
FQ [94]			X						X		X		X
IES [95]			X						X		X		X

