Note. *Adol.* adolescent, *Par.* parent, *TAU* treatment as usual, *CRT + TTP* cognitive remediation therapy + Teach the Parent, *CRT + FFT* cognitive remediation therapy + Family Fun Time, *EDE* Eating Disorder Examination, *EDE-Q* Eating Disorder Examination Questionnaire, *EDE-SF* Eating Disorder Examination Short Form, *ABOS* Anorectic Behavior Observation Scale, *BASC* Behavior Assessment System for Children-2, *WASI* Wechsler Abbreviated Scale of Intelligence, *D-Kefs* Delis-Kaplan Executive Functioning Scales (Trail Making, Verbal Fluency, Color-Word Interference, & Sorting), *BRIEF* Behavior Rating Inventory of Executive Function, *Rey-O* Rey-Osterrieth Complex Figure Test, *PennCNB* computerized neuropsychological battery, *C/E* Credibility/Expectancy Questionnaire, *MSCARED* Motivational Stages of Change for Adolescents Recovering from an Eating Disorder, *EDQoL* Eating Disorder Quality of Life, *DBS* Decisional Balance Scale, *CFS* Cognitive Flexibility Scale, *DFlex* Detail and Flexibility Questionnaire, *C-FOCI* Children’s Florida Obsessive Compulsive Inventory, *YBC-EDS-SRQ* Yale-Brown-Cornell Eating Disorders Self-report, *AFQ-Y* Action Fusion Questionnaire—Youth, *AAQ* Acceptance and Action Questionnaire, *AESED* Accommodation and Enabling Scale for Eating Disorders, *BIS/BAS* Behavioral Inhibition System and Behavioral Activation System Scales, *P-AAQ* Parental Acceptance and Action Questionnaire, *DASS-21* Depression Anxiety and Stress Scale-21, *FQ* Family Questionnaire, *IES* Impact of Events Scale

Randomization was obtained via block randomization using values from Research Randomizer, an online randomization program (http://www.randomizer.org/). An undergraduate research intern completed the randomization prior to recruitment starting, wrote the condition number on an index card, and sealed the index card in a security envelope. Envelopes are numbered consecutively. As participants consent to participate, they are assigned the next number and that envelope is pulled and put in their research chart. Once assessment is complete, the envelope is opened and the condition recorded in a password protected file.

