### Measurement strategy

As this is a pilot and feasibly RCT, we chose a comprehensive measurement battery that closely resembles batteries used in prior research investigating set-shifting, central coherence, and CRT in individuals with AN. See Table 4 for all measures and the measurement schedule. A goal of the study was to evaluate the utility of the battery and streamline it for future research. Both parents and the adolescent complete a standard self-report questionnaire battery, neuropsychological assessment, and IQ assessment. In addition, the adolescents complete a semi-structured diagnostic interview to assess eating disorder symptoms (Eating Disorder Examination, EDE [55]). We included measures designed to assist us in evaluating our outcome variables. As neurocognitive inefficiencies are hypothesized to be endophenotypes [7, 37], we included IQ and neuropsychological assessment of both adolescent and parents. Baseline assessment is comprehensive and typically lasts a significant portion of the day. Families are informed of the length of the intake during the screening phase.

As the adolescents are in hospital, the baseline assessment can occur over multiple days. For adolescents, the neuropsychological assessment is prioritized, as we want to be able to assess for any impairment that may be present when acutely underweight. Randomization occurs once neuropsychological assessment is complete; it is possible that the EDE and self-report may not be completed until after randomization. Parent neuropsychological and IQ assessment is scheduled at the parents’ convenience throughout the week that their child is in hospital. If parents are not able to complete the IQ assessment at baseline, it can be administered at 3 months post-discharge as parental IQ is expected to be stable.

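### Parents' baseline cognitive tests have no cut-off relative to randomization or the first parent session, so a TTP parent may be tested after practising a Stroop task

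*Protocol article*

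**What the plan says.** The article gives two accounts of when baseline ends.

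- **Blinding and randomization:** the adolescent is randomized after baseline assessment, and the envelope is opened once assessment is complete. From this the article concludes: "Research assistants completing the baseline assessment are therefore blind to the condition at baseline".
- **Measurement strategy:** "Randomization occurs once neuropsychological assessment is complete", directly after saying that the adolescent's testing has priority. The EDE and self-report may follow randomization. Parent neuropsychological and IQ tests are dealt with separately and may be done when it suits the parents, "throughout the week that their child is in hospital". No limit is set relative to randomization or to the parent sessions. Parent IQ alone gets a reason for lateness: "it can be administered at 3 months post-discharge as parental IQ is expected to be stable".

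Table 2 lists TTP session 1 as "Introduction to CRT + TTP Illusion task Infinity signs Stroop Geometric figure". The TTP description has adolescents "do four tasks with their parents". Family Fun Time (FFT) lists games, coloring and conversation, and treatment as usual (TAU) has no sessions.

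Table 4 gives parents the D-KEFS, Hayling, Rey-O and Brixton at baseline and again at 3 months. Its note lists the D-KEFS parts as "Trail Making, Verbal Fluency, Color-Word Interference, & Sorting".

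**The concern.** A baseline serves its purpose only if it is measured before the arms differ. Here the parent baseline can fall after the TTP arm has rehearsed material close to one of the tests. Only that arm is exposed, so the distortion does not cancel in a comparison with FFT or TAU.

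What is at stake is limited but real. The rationale section hypothesizes that CRT will "increase behavioral flexibility in adolescents and parents", and the secondary outcomes list changes in set-shifting or central coherence without restricting them to adolescents. The pilot is also meant to test its assessment procedures for a larger trial, so an open baseline window would be carried forward.

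Blinding is a second issue. The article says that research assistants open the envelopes and may recall a family's condition, and that they observe the TTP and FFT sessions. A parent tested late may therefore be tested by someone who knows the arm.

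**Working it through.** The plan gives no figure on test timing or practice, so there is none to reproduce on this point. Its power of .55 concerns the mixed MANOVA, whose dependent variables do not include parent cognition. It reproduces as 0.551 (df 8 and 110, noncentrality 2 × 60 × 0.25² = 7.5, alpha .10) and does not bear on the matter.

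**Step 1: can a parent test follow a TTP session?**

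From the article: weekday CRT, TTP at every other CRT session, parent sessions reviewed at CRT sessions 3, 5 and 7 (Table 1), and a median stay of 10 days. Assumed: randomization on hospital day 3 to 5, CRT starting on the next weekday, the first TTP session with CRT session 2, and a 10-day stay.

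Over all seven admission weekdays and these three randomization days, the first TTP session falls between day 5 and day 9. It is inside the stay in every case, so a parent test later in the stay can follow it.

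**Step 2: which tests overlap?**

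| Parent test | TTP counterpart in Table 2 | Link |
|---|---|---|
| D-KEFS Color-Word Interference | Stroop (session 1) | close |
| Rey-O | Geometric figure (sessions 1 and 2) | loose: describing a figure for another person to draw |
| Hayling, Brixton, other D-KEFS parts | none evident | none |

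**Step 3: direction.**

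Let g be the practice gain present at a late baseline, and h the part that remains at 3 months. Scores are oriented so that higher is better.

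- Clean baseline: change = h + other change.
- Late baseline: change = h − g + other change.
- Difference, late minus clean: −g, whatever h is.

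If a share p of TTP parents is tested late, the TTP mean change shifts by −p × g relative to a clean baseline. FFT and TAU shift by 0.

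**Step 4: size.**

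Neither p nor g is in the article. Assumed ranges: p from 10% to 75%, g from 0.1 to 0.5 SD.

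| p | g (SD) | shift = −p × g (SD) |
|---|---|---|
| 0.10 | 0.1 | −0.01 |
| 0.25 | 0.3 | −0.075 |
| 0.50 | 0.3 | −0.15 |
| 0.75 | 0.5 | −0.375 |

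For scale, with 20 per arm and an assumed baseline-to-follow-up correlation of 0.7, the standard error of a between-arm difference in change is √(2 × (1 − 0.7)) × √(2/20) = 0.775 × 0.316 = 0.245 SD. Most of the range is below one standard error.

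**Step 5: after the fix.** With p = 0 the shift is 0.

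**The case against.** **The text may already exclude it.** The Blinding and randomization section puts baseline before the envelope, and the Measurement strategy section names only the EDE and self-report as items that may come later. On a strict reading, parent tests are finished first. This has some force, but the sentence on parent testing is the specific rule and allows the whole hospital week. The two sections conflict and need reconciling.

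**Direction depends on what counts as effect.** If Stroop rehearsal is seen as test practice and not benefit, a clean baseline would itself flatter TTP at 3 months, and a practised baseline would partly cancel that. This is fair. The shift in Step 3 is an understatement only if rehearsal counts as part of what TTP delivers. On either view, an uncontrolled mix of early and late baselines in one arm is hard to interpret.

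**Exposure may be slight.** Stroop appears only in TTP session 1, and the research assistant need only see that at least two tasks are presented, so some parents may not do it. This stands and limits the size.

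**Stronger readings.** A reader might infer that the whole parent battery is contaminated, or that the flaw hides the effect the parent component is meant to have. The documents support neither. Only Color-Word Interference has a close counterpart. The main parent target is less symptom accommodation, measured by the AESED questionnaire, which task practice does not touch. The cognitive-flexibility hypothesis under Secondary aims names adolescents, and parent cognition is not among the MANOVA or growth-curve variables.

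**Conclusion.** The point holds as a minor one. The article permits a parent baseline taken after exposure in the TTP arm only, and contradicts itself on whether baseline is complete before randomization. For TTP parents tested late, change to 3 months on Color-Word Interference would tend to be understated, with a weaker possibility for Rey-O. The statement that baseline assessors are blind is not secured for parent testing.

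The size is unknown. The range of 0.01 to 0.375 SD rests wholly on assumed shares and practice gains, and the true value may lie at the low end. It would be tempting to express it as a fraction of some expected effect, but the article states no expected effect for parent cognition. The consequence is confined to secondary parent set-shifting and central-coherence data in a feasibility pilot. The feasibility outcomes, weight gain, engagement and accommodation are unaffected by this mechanism.

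**What to change.** Reconcile the Blinding and randomization section with the Measurement strategy section:

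1. Require parent executive-function tests before the envelope is opened, or at least before the family's first TTP or FFT session. Parent IQ may still be deferred.
2. Record each parent's test date, its position relative to randomization, and the number of parent sessions already held.
3. Handle late tests by one timing rule for all three arms, or in a sensitivity analysis. A rule anchored at the opening of the envelope is cleanest: it applies equally to TAU, which has no parent session, and it selects on something settled before the allocation is revealed.
4. Do not drop late-tested TTP parents alone. That is an arm-specific exclusion after randomization. If 25% to 75% were late, it would remove 5 to 15 of 20 TTP parents and none from the other arms.

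The cost is slightly less scheduling freedom for parents, in a study that wants to limit family burden, and some missing parent baselines. A parent session need not be held back for testing: a test not done in time is simply recorded as late.

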### Outcomes

The primary aim of the study is to evaluate the feasibility and pilot the procedures for an RCT of CRT with a family component delivered during a hospital stay for medical stabilization. Primary outcomes are as follows:Recruitment rates (% of patients admitted who are eligible, % enrolled). Ideally, we will be able to recruit 30% of those eligible and at least four adolescents and their parents a month.Completion rates (% of those enrolled who complete at least 6 sessions). Completion rates will vary based on the medically dictated hospital stay. As we have no control over when an adolescent will be discharged, completion rates will be combined with enrollment rates to determine how many participants would need to be enrolled in a future study (over-enrollment) to ensure the appropriate number of treatment completers.Refusal rates and reasons whyRetention rate (% of those enrolled who completed all assessment points, rate of drop out over 6 months of follow-up). Ideally, we would have a dropout rate < 25%. As adolescents are discharging to various levels of care, we track dropout rates and determine if we have higher rates associated with certain levels of care (e.g., residential treatment).Average length of time to complete measures

We will also pilot procedures and evaluate the following:Ease of record forms (can the study staff use forms effectively and can the interventionist easily record data needed from each CRT session)CRT task adaptations (e.g., are some tasks more difficult for adolescents, are there modifications that need to be made)Staffing needs (are there enough staff to recruit/enroll/assess/and administer CRT?)Acceptably of RCT to medical staff (evaluated through meetings with and feedback from staff (e.g., physicians, nurses, behavioral health)

In addition to piloting the study and assessing feasibility, our secondary goals are to examine relevant outcomes for a fully powered trial. We will examine the following:Willingness of adolescent to engage in treatment post-dischargeAdolescent rate of weight gain post-discharge to 6 monthsParental accommodation in symptoms post-discharge (group differences and over time changes)Changes in set-shifting or central coherence

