### Participants

Participants are male and female adolescents aged 12–18 who present in hospital for treatment of a restrictive eating disorder and at least one caregiver. Only adolescents who have not had prior multidisciplinary treatment for an eating disorder will be included. Inclusion and exclusion criteria are summarized in Table 3.^1^ The total enrollment is anticipated to be 60 adolescents.

**Table 3 Tab3:** Inclusion and exclusion criteria

Inclusion criteria	Exclusion criteria
• Adolescent is between 12 and 18 years of age and living at home with caregiver(s) • Adolescent meets diagnostic criteria for anorexia nervosa (either restricting or binge/purge subtype), or sub-threshold anorexia nervosa according to the DSM-5 criteria • Parent or primary caregiver is willing to participate in CRT + TTP or CRT + FFT sessions (if randomized to either condition) • Consent of all family members who will be participating in treatment • The adolescent is not currently receiving outpatient treatment for the eating disorder (i.e., their first presentation at CHOP)	• Caregiver or adolescent with a co-morbid diagnosis of psychotic disorder, substance dependence, substance abuse, or bi-polar disorder • Caregiver or adolescent with diagnosis of intellectual disability, developmental delay, or autism spectrum disorder • Adolescent with a diagnosis of feeding or eating concerns not elsewhere classified with primary symptoms of bingeing and purging, bingeing without compensatory behaviors, or spitting food with restricting patterns. • Adolescent with diagnosis of avoidant/restrictive food intake disorder • Adolescent or caregiver with acute suicide risk • Concurrent psychosocial treatment for another condition • Adolescent or parent (who will be participating) not fluent in English

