**Fig. 1 Fig1:**
[figure not shown]
Study flowchart/timetable for data collection

After consent is obtained and baseline assessment is completed, participants are randomized to one of three groups: CHOP’s standard care (treatment as usual; TAU), CRT + contact control (known as “Family Fun Time”), and CRT + Teach the Parent. Those randomized to one of the CRT conditions will receive individual sessions of CRT daily (excluding weekends) while in hospital. Follow-up will be naturalistic. All attempts will be made to follow participants whether they enter outpatient treatment or are referred to a higher level of care. Psychosocial, neurocognitive, medical, and behavioral measures will be collected throughout the study. Group differences will be evaluated at each of the five assessment time points.

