### Description of investigational intervention

The principles of cognitive remediation therapy are the same across studies; however, CRT protocols often vary in terms of the tasks used. This trial uses a modified version of an adolescent manual developed by [name] [47]. The CRT tasks included in our manual are delineated in Table 1. CRT sessions occur daily (excluding weekends) for 45–60 min every day while adolescents are in hospital, for up to 8 days. We have set an a priori definition of “treatment completion” as six sessions of CRT. Treatment completion for parent involvement component was set a priori at three sessions of either TTP or FFT. Though the median length of stay in hospital is 10 days, it is possible that adolescents may discharge before completing all sessions of CRT. These adolescents will continue to complete all study procedures (i.e., follow-up) but will not be considered treatment completers for feasibility assessment (what percentage of adolescents complete CRT) or data analysis (secondary goals).

Study interventionists include the PI or a graduate student under the PIs supervision. [name] provided initial training in CRT, and will provide supervision and feedback to the PI throughout the study duration. CRT sessions will be audio-recorded and coded for adherence to the manual. Should a study interventionist deviate from the manual (e.g., do tasks out of order), this will be noted in the data set. The interventionist will be informed and further training provided to ensure adherence.

CRT sessions are administered every weekday while the adolescent is in hospital, are conducted in an individual format, and tasks are delivered in a standard order to ensure consistency. Table 1 lists all tasks in the standardized order in which they are presented each session. Table 1 also notes the session in which the task occurs; most tasks are administered in each session. It is possible that not all tasks will be able to be administered due to time constraints or individual variables (i.e., hand flip if the adolescent has an IV). At the end of the pilot study, we will re-evaluate the tasks and determine if all should be included a final manual.

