#### Treatment at usual

Adolescents in this condition will not receive any experimental intervention. They will have a standard hospital stay with all normal contact with a multidisciplinary team of health professionals: attending physician, psychologist, social worker, and dietician. Medical stabilization for adolescents with AN at CHOP has been described elsewhere [51].

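### The primary completion rate is taken over all enrolled, including the TAU third who receive no CRT, so it cannot exceed about 67% and mixes deliverability with the allocation ratio

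*Protocol article*

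**What the plan says.** The Outcomes section of the protocol article defines the measure as "Completion rates (% of those enrolled who complete at least 6 sessions" and adds that "completion rates will be combined with enrollment rates to determine how many participants would need to be enrolled in a future study (over-enrollment".

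The Description of investigational intervention sets treatment completion "as six sessions of CRT" and refers to "feasibility assessment (what percentage of adolescents complete CRT". It names no denominator by arm.

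On who can receive sessions, the text accompanying the study flowchart says "Those randomized to one of the CRT conditions will receive individual sessions of CRT daily (excluding weekends) while in hospital". Of TAU, the section on that arm says "Adolescents in this condition will not receive any experimental intervention".

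On numbers, the Participants section says "The total enrollment is anticipated to be 60 adolescents", and the Power analysis section gives three groups of 20.

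The Discussion uses the enrolment rate and the percentage of treatment completers to judge how long a fully powered trial would take to recruit. It treats three years or more at one site as a reason to reconsider scale or the number of sites.

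**The concern.** A completion rate in a feasibility trial should say how often the intervention can be delivered to those assigned to it. With all enrolled adolescents as the denominator, the TAU adolescents count as non-completers by design. The result then depends on how many were allocated to TAU as well as on how well CRT was delivered. A reader who sees 50% cannot tell whether half of the CRT adolescents completed or three quarters did.

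The rate also feeds the planning of the next trial. A proportion with this trial's allocation ratio built into it carries over correctly only to a trial with the same share of CRT participants. The protocol does not fix the future allocation or the formula to be used.

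**Working it through.** **Inputs from the protocol.** 60 enrolled (Participants); 20 per arm (Power analysis); two of three arms receive CRT (Study design); no CRT in TAU (section on that arm); completion means at least six sessions (Outcomes; Description of investigational intervention); an ideal of at least four adolescents enrolled per month (Outcomes).

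**Assumptions.** The protocol gives no expected completion rate, so completion within the CRT arms, *c*, is set at 60%, 75% and 90%. A need for 100 CRT completers is used purely as an illustration.

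**The plan's own figure.** No completion figure is stated. The nearest computable figure that rests on the 3 × 20 layout is the MANOVA power. With f = .25, N = 60, alpha = .10, 8 and 110 degrees of freedom and noncentrality 0.25² × 2 × 60 = 7.5, power is 0.551, against the stated .55. The layout of 20 per arm is therefore consistent.

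**Ceiling.** (20 + 20)/60 = 66.7%. With the 40 CRT adolescents as denominator it would be 40/40 = 100%.

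**Rate as written** = 40*c*/60 = 2*c*/3:
- *c* = 60% is reported as 40%
- *c* = 75% is reported as 50%
- *c* = 90% is reported as 60%
- *c* = 100% is reported as 66.7%

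**Effect on over-enrolment.** Let K be the CRT completers needed and s the share of the future trial assigned to CRT. The correct enrolment is K/(s × *c*). The rate as written gives K/(2*c*/3). The ratio of the second to the first is s/(2/3) = 1.5s. For K = 100:

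| Use of the rate | s | Ratio | *c* = 60%: as written / correct | *c* = 75% | *c* = 90% |
|---|---|---|---|---|---|
| Total for a 1:1:1 trial, total CRT completers | 2/3 | 1.00 | 250 / 250 | 200 / 200 | 167 / 167 |
| Size of a CRT arm | 1 | 1.50 | 250 / 167 | 200 / 134 | 167 / 112 |
| Total for a two-arm 1:1 trial | 1/2 | 0.75 | 250 / 334 | 200 / 267 | 167 / 223 |

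**Effect on recruitment time.** At four enrolled per month under 1:1:1 and *c* = 75%, completers accrue at 4 × 2/3 × 0.75 = 2 per month. The rate as written gives 4 × 0.50 = 2, which is right for this allocation. Multiplying all four by the CRT-arm rate would give 4 × 0.75 = 3, which is too optimistic. A CRT-arm rate therefore has to be applied to the CRT share only.

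**The case against.** The strongest defence is that completers per enrolled participant is the natural quantity when the question is how many participants to enrol. For a trial with the same allocation it gives the correct total, as the first row of the table shows. The Secondary aims say that the hypotheses for the fully powered trial are the same three-group comparisons, so three arms may well be kept. This stands. A reader might infer that the definition always distorts the over-enrolment calculation, and the documents do not support that. The distortion depends on how the rate is used, and its direction changes with the design.

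A reader might also infer that a deliverable intervention could be declared undeliverable. No rule in the protocol would lead there. The Outcomes section gives targets for recruitment (30% of those eligible, four a month) and dropout (below 25%), but none for completion, which it describes as dependent on the medically determined stay.

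It can further be said that a CRT-arm denominator is what was meant, since "what percentage of adolescents complete CRT" comes in a discussion of adolescents discharged before finishing CRT. That is plausible, but it is not what the outcome definition says. The retention outcome in the same list uses the same base of those enrolled, and there it must cover all three arms because all are followed up. Either rate can be computed from the data collected, so no information is lost, but the stated primary outcome remains the one over all enrolled.

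Finally, the absence of a parent-session rate from the primary list is not an error. The Description of investigational intervention sets three parent sessions as a separate criterion for that component.

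**Conclusion.** The point holds as a fault in a stated definition. The primary completion rate has a ceiling of about 67% and reports two thirds of true CRT completion, whatever the quality of delivery. Both figures assume exactly 20 per arm; a small imbalance would shift them slightly.

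The consequence for planning is conditional. There is no error if the next trial is again 1:1:1 and counts total CRT completers. There is a 1.5-fold excess if the rate is used to inflate a CRT arm, and a shortfall to 0.75 of the required number if it is read as total enrolment for a two-arm 1:1 trial. These ratios do not depend on the assumed completion rate or on the illustrative 100 completers. Because the protocol fixes neither the future design nor the formula, nothing in it guarantees the harmless case.

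**What to change.** In the Outcomes section, define the completion rate as adolescents with at least six CRT sessions divided by adolescents randomised to CRT + TTP or CRT + FFT, reported per arm and pooled.

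State with it how the rate enters the over-enrolment and recruitment-time calculations: apply it to the CRT arms only, then add the TAU arm according to the future trial's allocation. Without this second step, the corrected rate would understate total enrolment. In the 1:1:1 example at 75%, 134 would be read as the total when 200 are needed.

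The cost is a line or two of text and no new data. The estimate rests on about 40 adolescents instead of 60, but the TAU adolescents carry no information on whether CRT can be completed. Reporting the criterion of at least three parent sessions on the same denominator is optional.
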